### Study design

The present clinical protocol is designed as a double-blind, parallel, non-inferiority, randomized clinical trial.

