### Sample size estimation

The sample size calculation for this study was conducted through *a priori* power analysis using G*Power 3.1.9.7 (29). Parameters were chosen, including α = 0.05 and power (1-ß) = 0.95. An effect size of f = 0.1 was selected based on previous research findings (15). Specifically, in the intent-to-treat sample (N = 73), 18 participants (51.4%) in the MST group (N = 35) and 16 (42.1%) in the ECT group (N = 38) met response criteria, while 13 (37.1%) in the MST group and 10 (26.3%) in the ECT group met remission criteria. In addition to the two experimental conditions (MST and ECT), covariates including age, sex, duration of illness, age of onset, intelligence quotient (IQ), and antidepressant usage were considered, resulting in a total of 6 covariates. Accounting for a potential dropout rate of 20%, the final estimated number of participants required for the study was determined to be 210. (**Figure 2**).

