### Outcomes

#### Primary outcome

The primary outcome measure is the change in HDRS-24 total score from baseline to the 12-week follow-up, which is assessed after the completion of the 12-session acute treatment phase (conducted over 4 weeks) and a subsequent 12-week post-treatment observation period. A reduction of at least 50% in the HDRS-24 score indicated a response to treatment, while a reduction of at least 60% in the HDRS-24 score and a total score of 8 or less indicated remission. Change in HVLT-R total recall score from baseline to the 12-week follow-up (assessing verbal memory, a key cognitive domain sensitive to seizure therapy effects).

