## Data entry and analyses

This trial aims to provide replicated evidence that MST is as effective as ECT in terms of remission rates, response rates, and reduction of depressive symptoms (assessed by the primary outcome: change in HDRS-24 from baseline to 12-week follow-up after the acute treatment phase) and superior in preserving verbal memory (via HVLT-R as an additional primary outcome), with fewer physical and cognitive side effects overall. Additionally, this study will explore personalized electrophysiological indicators (EEG/ECG) in an exploratory manner to inform future individualized treatment decisions for ECT and MST, and to generate hypotheses about the physiological mechanisms underlying the antidepressant efficacy and cognitive effects of MST/ECT. To our knowledge, this will be the largest RCT comparing ECT and MST in China. The trial will provide evidence to determine whether individualized treatment decisions based on personalized electrophysiological characteristics hold promise for optimizing the balance between efficacy and side effects (40). Specifically, it will offer insights into the potential effect sizes, acceptability, feasibility, and safety of the novel interventions under investigation. Predicting efficacy and side effects based on physiological characteristics, such as indicating greater side effects with ECT and comparable efficacy but fewer side effects with MST for patients with MDD, suggests that MST may be more suitable for these patients. Alternatively, physiological characteristics indicating superior efficacy with ECT compared to MST, with comparable side effects between the two, suggest that ECT may be more appropriate for these patients.

Firstly, data entry will undergo a thorough double-check to ensure accuracy. Data quality will then be assessed, with particular attention given to data distribution, and outliers will be excluded from subsequent analysis. Once data integrity is confirmed, detailed analyses of primary and secondary outcomes will be conducted using IBM SPSS Statistics 20 for Windows (Armonk, NY: IBM Corp).

Descriptive statistics, such as mean and standard deviation, will be computed for each study arm separately. Analyses will be performed within the intention-to-treat (ITT) framework to assess the effectiveness of interventions for all participants, utilizing multiple imputed datasets to address missing data.

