Appropriate statistical methods will be employed for data analysis, including mixed-effects models for repeated measures (MMRM). MMRM with a factorial design (3 time points × 2 conditions) will be conducted to examine significant interactions between time (baseline, Day 30, and Week 12) and condition (ECT and MST), while adjusting for potential covariates such as age, sex, duration of illness, age of onset, IQ, and antidepressant usage. This approach is robust to missing data under the missing-at-random (MAR) assumption and provides unbiased estimates of treatment effects. The significance level will be set at 0.05.

Sensitivity analyses will be performed to assess the robustness of results to missing data, including multiple imputation (MI) under MAR and missing-not-at-random (MNAR) assumptions. Results from MMRM and MI will be compared. Exploratory analyses will include subgroup analyses by demographic/clinical characteristics and correlation analyses between neurophysiological biomarkers (EEG/ECG) and treatment outcomes, using linear or logistic regression models as appropriate.

Subgroup analyses will compare relapse rates and time-to-relapse between participants who received maintenance treatments versus those who did not, within both MST and ECT groups. This will help disentangle the effects of acute treatment from post-treatment management strategies.

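### A declared non-inferiority trial whose only named between-arm test, and whose sample size, are for detecting a time × condition difference

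*Protocol article*

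**What the plan says.** **Design and aim.** The title, Study objectives and Study design all use the term non-inferiority; the trial is "designed as a double-blind, parallel, non-inferiority, randomized clinical trial". Under Data entry and analyses the aim is stated as: "This trial aims to provide replicated evidence that MST is as effective as ECT in terms of remission rates, response rates", followed by reduction of depressive symptoms, together with superiority in preserving verbal memory.

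**Primary outcomes.** "The primary outcome measure is the change in HDRS-24 total score from baseline to the 12-week follow-up". A second one is added under the same heading: "Change in HVLT-R total recall score from baseline to the 12-week follow-up".

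**Analysis.** Data entry and analyses describes an MMRM with three time points and two conditions, which "will be conducted to examine significant interactions between time (baseline, Day 30, and Week 12) and condition (ECT and MST"), adjusted for covariates. Then: "The significance level will be set at 0.05".

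**Sample size.** "Parameters were chosen, including α = 0.05 and power (1-ß) = 0.95", with f = 0.1. The Figure 2 legend identifies the test as a within-between interaction in a repeated-measures ANOVA (2 groups, 6 measurements, correlation 0.5, sphericity correction 1). It gives a total of 166. Sample size estimation raises this to 210 for 20% dropout.

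The article states no non-inferiority margin, no non-inferiority null hypothesis and no confidence bound to be compared with a margin.

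**The concern.** A non-inferiority trial has to reject the hypothesis that the new treatment is worse by at least a stated margin. The interaction test has a different null hypothesis, namely that the two condition profiles over time are parallel. Failing to reject that null may only mean that the data were too weak. Rejecting it shows that the profiles differ somewhere, but not which arm did better or at which visit.

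A margin on its own could be left to a statistical analysis plan. Here the article goes further: it names a test and sizes the trial for the same kind of test, and both look for a difference. An analysis plan could repair this only by replacing what the article says.

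At stake is the headline efficacy conclusion. If a non-significant interaction were reported as comparable efficacy, fewer patients or noisier data would make that report more likely.

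**Working it through.** **1. Reproduce the stated sample size.** Inputs from the Figure 2 legend: f = 0.1, m = 6 measurements, k = 2 groups, ρ = 0.5, ε = 1, α = 0.05.

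- λ = N f² m / (1 − ρ) = 166 × 0.01 × 6 / 0.5 = 19.92
- df = (k − 1)(m − 1) = 5 and (N − k)(m − 1) = 164 × 5 = 820
- Critical F = 2.225, power = 0.950. N = 164 gives 0.947, so 166 is the minimum.
- Dropout: 166 / 0.8 = 207.5, so 208, which 7 centres × 30 rounds to 210.

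The figure reproduces. It is the sample size of a test for a difference; f = 0.1 is an effect to be detected, not a margin.

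**2. What a non-significant result would mean.** Assumptions: 168 analysed (210 × 0.8), three time points as in the analysis section, the plan's ρ of 0.5, and MST truly worse by D (in SD) at both Day 30 and Week 12. With ρ = 0.5 the SD of a change score is √(2(1 − 0.5)) = 1 raw SD, so raw and change units coincide.

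- f = SD(0, D, D) / 2 = D√2 / 6
- λ = 168 × f² × 3 / 0.5, df = 2 and 332, critical F = 3.023

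| True deficit D | f | λ | P(non-significant) |
|---|---|---|---|
| 0.2 SD | 0.0471 | 2.24 | 0.753 |
| 0.3 SD | 0.0707 | 5.04 | 0.497 |
| 0.4 SD | 0.0943 | 8.96 | 0.235 |

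With less information the probability rises. At D = 0.3 SD it is 0.40 for N = 210, 0.50 for N = 168 and 0.68 for N = 100.

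**3. What a significant result would mean.** The F test has no sign: λ is the same for D and −D. It also pools the two post-baseline visits. If the arms differ by 0.4 SD at Day 30 and not at all at Week 12, the profile (0, D, 0) has the same SD as (0, D, D), so λ is again 8.96. The test is then significant with probability 1 − 0.235 = 0.765, although the primary quantity, change to Week 12, shows no difference.

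**4. What the present size can support as a non-inferiority test.** Assumptions: one-sided 0.025 (the limit of a two-sided 95% CI), true difference zero, 84 evaluable per arm.

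- Standard error = √(2/84) = 0.154 SD
- Smallest testable margin = (1.960 + z_power) × 0.154
- 80% power: (1.960 + 0.842) × 0.154 = 0.43 SD
- 90% power: (1.960 + 1.282) × 0.154 = 0.50 SD
- 95% power: (1.960 + 1.645) × 0.154 = 0.56 SD

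Under the same assumptions at 95% power, a margin of 0.5 SD needs 208 evaluable (260 enrolled), 0.4 SD needs 326 (408) and 0.3 SD needs 578 (723). At 80% power the enrolled totals are 158, 248 and 438. The article gives neither a margin nor an SD for HDRS-24 change, so only this range can be shown.

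**The case against.** The best defence is that the article's list of methods is open, the interaction test is never labelled primary, and nothing says that a non-significant interaction will be read as non-inferiority. The margin and decision rule may sit in the full protocol or analysis plan. The first part stands: the false reading in step 2 is what the named test invites, not a rule the article states. The second part is weakened by the sample size, which targets a difference as well.

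A second defence also stands in part. With baseline as reference, the Week 12 component of the interaction is exactly the MST-minus-ECT difference in change to Week 12. The model and the primary quantity are therefore sound; the fault is the omnibus test and the lack of anything to compare the contrast with.

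A reader might infer three stronger points that the document does not support:

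- **That a confidence-interval rule would cut 75%, 50% and 24% to 2.5%.** These are unlike quantities. The 2.5% applies at a true deficit equal to the margin. With an assumed 0.5 SD margin and 84 per arm, the CI rule would itself declare non-inferiority with probability about 49%, 25% and 9% at deficits of 0.2, 0.3 and 0.4 SD. Whether those would be false claims depends on a margin that has not been given.
- **That two primary outcomes at 0.05 each give 1 − 0.95² = 9.75% family-wise error.** This needs independent outcomes that can be claimed separately. They are measured in the same patients, and the aim joins them with an 'and'. If both must succeed, the level is not inflated.
- **That non-inferiority should also be shown in the completers defined under ECT and MST procedures.** That set includes patients who remit before the eighth treatment, so membership depends on outcome and it is not a neutral per-protocol check.

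**Conclusion.** The mismatch is real and must be fixed. The declared design and intended conclusion are non-inferiority; the only named between-arm test and the sample size address a difference. As written, no result of the named test can establish that MST is non-inferior to ECT on HDRS-24.

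The 75%, 50% and 24% rest on 168 analysed, ρ = 0.5 and equal deficits at both post-baseline visits. They support one statement only: non-significance is not evidence of non-inferiority. They are not the error rate of a rule the article has adopted. The fault concerns the efficacy claim; a difference test remains suitable for HVLT-R superiority.

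**What to change.** - **Decision quantity.** Keep the MMRM. For HDRS-24, let the decision rest on its Week 12 contrast, MST minus ECT in change from baseline, with a two-sided 95% CI. The time × condition interaction can stay as a descriptive result.
- **Rule.** Declare non-inferiority only if the limit unfavourable to MST lies inside a margin in HDRS-24 points that is clinically justified and fixed before unblinding.
- **Sample size.** Restate the justification and power for this test, with the margin and the assumed SD of change. The margin must not be chosen to fit N. Unless a margin of about 0.56 SD or more can be justified, the stated 95% power has to be lowered or more patients recruited.
- **Second primary outcome.** State how the 0.05 level is shared with HVLT-R superiority. Testing it only after HDRS-24 non-inferiority is met is one option; it costs no alpha, but HVLT-R could then not be claimed if non-inferiority fails.

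**Cost.** Protocol and analysis plan wording and a registry update, with no new measurements. The open cost is sample size: at 80% power, 210 enrolled would suffice for a 0.5 SD margin (158 needed) but not for 0.4 SD (248 needed). With the trial planned to run to December 2027, this is best settled now.

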**Figure 2 f2:**
[figure not shown]
G*Power-based sample size calculation for a repeated-measures ANOVA with a within-between interaction. The plot depicts an *a priori* power analysis to determine the required sample size for a repeated-measures analysis of variance examining the interaction between a between-subjects factor (2 groups) and a within-subjects factor (6 measurement time points). The upper panel shows the central F-distribution under the null hypothesis (red solid curve) and the noncentral F-distribution under the alternative hypothesis (blue dashed curve). The critical F-value (2.22502) is indicated by the green vertical line. The red shaded region represents the α error probability (Type I error, set at 0.05), and the blue shaded region denotes the β error probability (Type II error), with power (1−β) targeted at 0.95. Input parameters include: effect size (f) = 0.1, α = 0.05, number of groups = 2, number of repeated measurements = 6, correlation among repeated measures = 0.5, and sphericity correction (ϵ) = 1. Output parameters reveal a total required sample size of 166, a noncentrality parameter (λ) of 19.92, numerator degrees of freedom (df) = 5, denominator df = 820, and an actual power of ~0.95.

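### HVLT-R superiority is defined at Week 12, but the only between-arm test named is a two-degree-of-freedom time-by-condition interaction that a Day 30 difference alone could make significant

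*Protocol article*

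**What the plan says.** Three statements in the protocol article bear on this.

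- *Outcome.* The Primary outcome section adds a second measure at one visit: "Change in HVLT-R total recall score from baseline to the 12-week follow-up".
- *Claim.* Data entry and analyses says the trial is to show MST "superior in preserving verbal memory (via HVLT-R as an additional primary outcome"), alongside comparable antidepressant efficacy.
- *Test.* The same section says "MMRM with a factorial design (3 time points × 2 conditions) will be conducted", its purpose being "to examine significant interactions between time (baseline, Day 30, and Week 12) and condition (ECT and MST"), with adjustment for six covariates. It then states: "The significance level will be set at 0.05".

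No Week 12 contrast is named, and nothing says how the interaction result leads to the superiority claim. The sample size is also built on an interaction test: the Figure 2 legend describes a within-between interaction in a repeated-measures ANOVA, there with six time points.

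**The concern.** The claim concerns one visit. The named test concerns two visits jointly. With three time points and two arms, the interaction has (3 − 1) × (2 − 1) = 2 degrees of freedom, and its null is that the arms change equally from baseline to Day 30 and from baseline to Week 12. A difference at either visit is enough to make that null false. Rejecting it does not show that the arms differ at Week 12, so a 0.05 level on the interaction is not a 0.05 level for the Week 12 claim.

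The case that matters is a memory difference at the end of treatment that has closed by Week 12. Day 30 is the last treatment day in Table 1, and assessments take place three hours after the session, so an acute difference there is plausible. If the interaction were read as the primary result, an acute effect could be reported as better-preserved memory at 12 weeks. The point applies to the superiority claim on HVLT-R. The non-inferiority claim on HDRS-24 is a separate matter.

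**Working it through.** **1. The plan's own figure.** The inputs are "Parameters were chosen, including α = 0.05 and power (1-ß) = 0.95" (Sample size estimation), and "Input parameters include: effect size (f) = 0.1, α = 0.05, number of groups = 2, number of repeated measurements = 6" and "correlation among repeated measures = 0.5, and sphericity correction (ϵ) = 1" (Figure 2 legend).

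- λ = f² × N × m / (1 − ρ) = 0.01 × 166 × 6 / 0.5 = 19.92.
- Degrees of freedom: (2 − 1)(6 − 1) = 5 and (166 − 2)(6 − 1) = 820.
- Critical F = 2.2250; power = 0.9501.
- Dropout: 166 / 0.8 = 207.5, so 208. The stated 210 is 7 centres × 30.

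The stated figure reproduces. It confirms that an interaction F test was the planning test.

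**2. Inputs for the check.**

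- From the article: 105 per arm; 20% dropout, so 105 × 0.8 = 84 per arm; ρ = 0.5 (the Figure 2 planning value).
- Assumed, because the article gives no HVLT-R SD, expected difference or correlation: equal SDs, compound symmetry, ρ = 0.7 as a sensitivity value, Day 30 gaps of 0.2, 0.3 and 0.5 SD, and a true Week 12 difference of zero.

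**3. Formulas.** In SD units, each change from baseline has variance 2(1 − ρ), and the two changes have covariance (1 − ρ). For between-arm differences d = (d30, d12) and n per arm, the joint test has noncentrality (n/2) d′S⁻¹d on 2 and 2n − 3 degrees of freedom. With d = (x, 0) this reduces to

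λ = n x² / [3(1 − ρ)].

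For n = 84 and ρ = 0.5, λ = 84x² / 1.5 = 56x². That is 2.24, 5.04 and 14.0 for x = 0.2, 0.3 and 0.5. The critical F on 2 and 165 df is 3.051.

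**4. Probability that the interaction is significant when the Week 12 difference is zero.**

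| Per arm | ρ | gap 0.2 SD | gap 0.3 SD | gap 0.5 SD |
|---|---|---|---|---|
| 84 | 0.5 | 24.5% | 49.9% | 92.3% |
| 84 | 0.7 | 38.5% | 73.2% | 99.4% |
| 105 | 0.5 | 29.8% | 60.0% | 96.9% |

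The 1-df Week 12 contrast rejects in 5% in every cell (2.5% in favour of MST). Simulation at 84 per arm and ρ = 0.5 (10,000 runs) gave 24.2%, 49.6% and 92.2% for the interaction and 5.0%, 4.9% and 5.2% for the contrast. In a separate simulation of 20,000 runs with a gap of 0.5 SD, 87% of trials combined a significant interaction with a non-significant Week 12 contrast.

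**5. Price of using the contrast.** If the difference exists only at Week 12 (84 per arm, ρ = 0.5), contrast versus interaction power is 25.2% v 24.5% at 0.2 SD, 48.9% v 49.9% at 0.3 SD, 73.1% v 76.1% at 0.4 SD and 89.6% v 92.3% at 0.5 SD. The largest loss in these four cases is about 3 points.

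**The case against.** The strongest reply is that the decision rule is inferred. The analysis section presents MMRM as one of the methods to be used, does not mention HVLT-R when it describes the interaction, and never calls the interaction the success criterion. The endpoint section fixes Week 12, the fitted model yields the Week 12 difference, and naming that contrast is ordinary content for an analysis plan that is not shown here. To report preserved memory at 12 weeks with no difference at 12 weeks, the investigators would have to ignore their own Week 12 estimate.

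Much of this stands, and it limits the point in four ways.

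- A reader might infer that a Day 30 gap would yield a positive primary result. The article does not say so, and at assumed gaps of 0.2 and 0.3 SD the interaction is significant in only about a quarter and a half of trials. Could is the right word.
- A reader might infer that an on-treatment gap that later closes is the expected pattern. The section on comparative side effects reports more confusion and slower reorientation after ECT. Those are not HVLT-R recall, and the same section calls trial results on cognition inconsistent and cites a study with no cognitive side effects in either arm.
- A reader might object that the test has no direction. That adds little: a two-sided contrast also needs its estimate read for direction, and the proposed remedy is itself two-sided.
- The rejection rates depend on assumed gaps and correlations.

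The reply fails on one matter. The article does not merely leave the test open. It names a specific effect, the visits and the level, and it sizes the trial on an interaction as well. An analysis plan that followed this text would carry the mismatch forward.

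**Conclusion.** The point holds in limited form and should be fixed. The article gives a primary superiority claim at Week 12 and names no test that addresses Week 12 on its own. The test it does name does not hold the error rate for that claim at 5% when the arms differ at Day 30. With 84 per arm and ρ = 0.5, the chance of a significant interaction without any Week 12 difference runs from about 24% (gap 0.2 SD) to 92% (gap 0.5 SD). It is higher with ρ = 0.7 or with all 105 per arm. If there is no difference at either visit, the interaction keeps its nominal 5%, so the problem arises only when a Day 30 difference exists. Whether one will exist, and how large it would be, cannot be settled from the article.

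**What to change.** In Data entry and analyses, state that HVLT-R superiority is judged from one contrast in the planned MMRM: the MST minus ECT difference in change from baseline to Week 12, tested two-sided at 0.05, reported with its 95% CI, and claimed only if it favours MST. Report the Day 30 contrast as a secondary result describing the acute memory effect, and the overall interaction as supportive.

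This takes a sentence or two of text and uses the same model and data, with no extra participants. There are two costs: up to about 3 points of power for a difference present only at Week 12, and a difference seen only at Day 30 no longer counts towards the primary claim. The change should be made before unblinding.

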### Randomization procedure and blinding

A permuted block randomization method will be utilized to allocate participants to treatment groups at each study site. The sample size was consistent across sites, with 50% of participants assigned to receive ECT and the remaining 50% allocated to receive MST. Both clinical staff and participants were blinded to the treatment assignment. Randomization numbers were sealed in opaque envelopes, which were opened by the designated seizure therapy technician responsible for administering either ECT or MST treatment, based on the randomization numbers, only at the start of treatment. Randomization occurred on Day 1 immediately following baseline data collection. Following completion of the intervention, participants will be asked to provide feedback on whether they believe they received ECT or MST stimulation.

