### Assessments

#### Clinical measures

Clinical assessments will be administered by blinded raters at various time points throughout the study, including baseline, post-session 3, 6, 9, and 12 (3 hours after each session), as well as at the 4-week, 8-week, and 12-week follow-up visits. The primary outcome measure was the total score on the 24-item Hamilton Depression Rating Scale (HDRS-24) (28). Additionally, the Hamilton Anxiety Scale (HAMA) (30), clinician-rated, served as a secondary outcome measure. Other assessments included self-reported measures such as the Self-Rating Depression Scale (SDS) (31) and the Self-Rating Anxiety Scale (SAS) (32), as well as clinician-rated measures including the Global Assessment of Functioning (GAF) scale (33). Follow-up assessments were conducted monthly. Prior to the commencement of the experiment, all subjects will undergo an interview using the MINI-International Neuropsychiatric Interview (M.I.N.I. 5.0) (34). Additionally, participants filled out a self-administered questionnaire to provide demographic information.

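### The stated primary model compares change scores without adjusting for baseline HDRS-24, does not name site, and uses three of eight assessments: unbiased, but less efficient than the data allow

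*Protocol article*

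**What the plan says.** The Data entry and analyses section of the protocol article specifies a mixed model for repeated measures with two conditions and three times: baseline, Day 30 and Week 12. The effect examined is the time-by-condition interaction, "while adjusting for potential covariates such as age, sex, duration of illness, age of onset, IQ, and antidepressant usage". The Sample size estimation section names the same variables and counts them: "antidepressant usage were considered, resulting in a total of 6 covariates". Neither list contains site or baseline HDRS-24.

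On allocation, the Randomization procedure and blinding section says: "A permuted block randomization method will be utilized to allocate participants to treatment groups at each study site". There are seven sites with 30 patients each.

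HDRS-24 is collected more often than it is modelled. The Clinical measures section schedules assessments "including baseline, post-session 3, 6, 9, and 12 (3 hours after each session), as well as at the 4-week, 8-week, and 12-week follow-up visits", which makes eight. The primary efficacy outcome is the change in HDRS-24 from baseline to the 12-week follow-up. Change in HVLT-R total recall over the same interval is an additional primary outcome.

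**The concern.** Three features of the model leave information unused.

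- **Baseline.** It is a level of the response and the arms may differ there, so the model does not use the fact that randomisation makes the baseline means equal in expectation.
- **Site.** It is the blocking factor but not a term in the model, so the standard error does not reflect the design.
- **Visits.** Scores after sessions 3, 6 and 9 and at follow-up Weeks 4 and 8 do not enter. A patient lost after Week 4 or Week 8 contributes nothing later than Day 30.

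The Study design section calls this a non-inferiority trial. There the width of the interval decides success, so avoidable width is a cost to the sponsor. It does not favour the new treatment.

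**Working it through.** **1. The plan's own figure.** Inputs from Sample size estimation and Figure 2: "Parameters were chosen, including α = 0.05 and power (1-ß) = 0.95", f = 0.1, two groups, and "number of repeated measurements = 6, correlation among repeated measures = 0.5". For the within-between interaction, λ = f² × N × m / (1 − ρ) = 0.01 × 166 × 6 / 0.5 = 19.92, with df 5 and 164 × 5 = 820. The critical F is 2.22502 and the power 0.9501. So 166 reproduces. Then 166 / 0.8 = 207.5, rounded up to 208, and 7 × 30 = 210. I take ρ = 0.5 from here. It is one planning input for six measurements, not an estimated correlation between baseline and Week 12.

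**2. What the stated model estimates.** Arm means are free at all three times. With complete data, the Week 12 interaction contrast is therefore the difference between arms in mean change. Covariates entered as main effects shift all of a patient's values equally and cancel from that contrast. The same holds for site entered as a main effect in this model.

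**3. Baseline adjustment.** Let σ0 and σ1 be the baseline and Week 12 SDs. Per patient:

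- change score: σ0² + σ1² − 2ρσ0σ1
- baseline-adjusted: σ1²(1 − ρ²)
- difference: (σ0 − ρσ1)², which is never negative

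Take σ1 = 1, r = σ0/σ1 and ρ = 0.5. The half-width is 1.96 × √(2V/84), with 84 completers per arm (210 × 0.8 / 2), in Week 12 SDs. The values of r are assumptions.

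| r | V, change | V, adjusted | Cut | 95% half-width |
|---|---|---|---|---|
| 1.0 | 1.00 | 0.75 | 25% | 0.302 to 0.262 |
| 0.8 | 0.84 | 0.75 | 10.7% | 0.277 to 0.262 |
| 0.6 | 0.76 | 0.75 | 1.3% | 0.264 to 0.262 |
| 0.5 | 0.75 | 0.75 | 0% | 0.262 to 0.262 |

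Entry requires HDRS-24 of at least 18 and Week 12 has no such floor, so r below 1 is plausible. With r = 1 and other assumed correlations, the cut is 35% at ρ = 0.3 (1.40 to 0.91), 15% at 0.7 (0.60 to 0.51) and 10% at 0.8 (0.40 to 0.36).

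**4. Site.** A site effect that is constant over time cancels from a change contrast. Only the between-site share s of the variance in change matters. If it is ignored, the SE is too large by the factor 1/√(1 − s). The article gives no value, so s is assumed:

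| s | SE too large by | True two-sided level at nominal 0.05 |
|---|---|---|
| 0.01 | 0.5% | 0.049 |
| 0.05 | 2.6% | 0.044 |
| 0.10 | 5.4% | 0.039 |

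**5. Visits.** I compared the asymptotic variance of the Week 12 contrast using three visits and all eight, with equal SDs, compound-symmetric (0.5, 0.7) or first-order autoregressive (0.7, 0.8) correlation, and 20% monotone dropout placed in different ways.

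- Complete data: no gain in any case.
- Unadjusted for baseline: the cut is 1% (autoregressive 0.7, even dropout, 2.070 to 2.046) to 5% (autoregressive 0.8, all loss at Week 12, 1.765 to 1.671).
- Baseline-adjusted: 2% to 8% (the largest is 1.140 to 1.046).

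**The case against.** The best defence is that this is a condensed article. The covariates are introduced as examples, the mixed model is offered as one of the appropriate methods, and a fuller analysis plan may name site and baseline. For site this carries weight: it is unnamed, not shown to be excluded, although the sample size section does count exactly six covariates. For baseline it does not help. The article fixes baseline as a response level, and a longer covariate list does not change that. The three times are also fixed explicitly.

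It is also fair to say that baseline is not ignored. A difference in change matches the declared outcome and is unbiased under randomisation. The criticism is one of efficiency.

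Several stronger readings are tempting, and the documents do not support them.

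- *The model wastes the equivalent of a third more patients.* The ratio 1/0.75 = 1.33 needs equal SDs and ρ = 0.5 between baseline and Week 12. No SD is given, and the entry floor makes a smaller baseline SD plausible.
- *Omitting site makes the test invalid.* Any error is conservative.
- *Dropping five visits discards much precision.* The gain is nil with complete data and small otherwise. The planned multiple imputation might also use those visits, since its variables are not stated.
- *Power falls to 0.81.* Putting three times into the plan's formula gives λ = 0.01 × 166 × 3 / 0.5 = 9.96 and power 0.81. But f = 0.1 is not the same effect at a different number of times, and that test is not the Week 12 contrast.
- *Age, age of onset and duration are redundant and widen the interval.* Duration is not defined, and a redundant covariate leaves the treatment SE essentially unchanged.
- *The trial will miss non-inferiority.* The article gives neither a margin nor an SD, so this cannot be quantified.

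**Conclusion.** The point holds as a modest one about efficiency. The stated primary contrast is an unadjusted difference in change, from a model that does not name the randomisation stratum and uses three of eight assessments. It is unbiased under randomisation.

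Baseline adjustment is the only element that could matter much. At ρ = 0.5 it removes between 0 and 25% of the contrast variance as the baseline SD goes from half of the Week 12 SD to equal to it. Asymptotically it never loses precision. Site costs a few percent of SE at most over the shares tabulated, in the conservative direction, and only through between-site variance in change. The extra visits are worth including mainly because they make the missing-at-random assumption, on which the section relies, more credible. These sizes rest on assumed SD ratios, site shares, correlation patterns and dropout patterns, none of which the article supplies.

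**What to change.** Specify the primary model for HDRS-24 as a mixed model for repeated measures on the post-baseline scores at all scheduled visits. Its terms are arm, visit, arm by visit, baseline HDRS-24, baseline by visit, and site. The arm difference at Week 12 is the primary contrast. A model that keeps baseline as a response and constrains the arm means to be equal there is an acceptable alternative. It then needs site by visit, because a site main effect would cancel from the change.

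Use the same form for HVLT-R with its own baseline; cognitive tests follow the clinical assessment schedule.

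The cost is wording in the analysis plan, settled before unblinding. Every variable is already collected, and no patients or visits are added.
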